**Fig. 2 Fig2:**
[figure not shown]
Flow diagram of ‘Learn to Dare!’ study

Parents (and children, when they are 12 or older) send a signed informed consent form to our university, after which they receive an automatically generated e-mail with their account information. With this account, the children have access to the screening questionnaire on the platform. The authors that will be responsible for data analyses do not have access to the accounts and are completely blinded from participants’ information.

We use the Youth Anxiety Measure for DSM-5 (YAM-5, [54, 55]) as a screening tool and to measure the development of anxiety over time. When completing the YAM-5, children also fill in their demographic features. Children who score in the highest quartile are labelled as high-anxious. We use different cut-offs for boys and girls in order to increase the chance of a proportional influx of boys and girls. All other children are excluded and receive a message that they are not severely anxious, and that the program is not intended to suit their level of anxiety. These children receive links to general anxiety websites for children.

Consecutively, the high-anxious children are invited by e-mail to book a date for a diagnostic interview. The diagnostic interview Structured Clinical Interview for DSM-5 Disorders for Children (SCID, [56]) is performed by telephone with a trained interviewer. If the SCID shows that a child suffers from a severe anxiety disorder other than specific phobias, the child is excluded from the study. In this case, the first author does get access to the accounts of the participants (unblinding) as the parents are contacted by phone. Parents are advised by the first author to seek help for their child at a local mental health care institution.

The study concerns a randomized controlled trial (RCT). Within the ‘Learn to Dare!’ platform, the included high-anxious children are automatically randomized to the intervention group or to the waitlist control group. Children in the waitlist control group can participate in the intervention too after the last assessment point. We apply block randomization with child’s age and sex as strata. If children are randomized to the intervention group, they are assigned personal trainer who helps them during the training. The intervention and assessments are aimed at the children only.

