To test the primary research question, we will use regression model with the outcome Anxiety Level (AL) as dependent variable and condition (LTD vs WL) as predictor. Sex and Age will be added as extra predictors, plus interactions between predictors to see if the effects differ per sex and age category (LC). Model: AL = b0 + b1*Group + b2*Sex + b3*LC + b4*Group*Sex + b5*Condition*LC. To test the moderation and mediation models, we will use multilevel analysis [64]. The five assessments (T1,T2,T3,T4,T5) will be the lowest level, the children the second level. This model can be considered a moderated mediation model (Hayes, 2013). The mediation analysis will consist of 2 steps. 1st: Dysfunctional Cognitions (DC) and Avoidance Behavior (AB) will be dependent variables, in separate analyses. 2nd: Anxiety level (AL) will be the dependent variable. Time will be added and modelled as T = 0,1,2,3,4, to tested the linear increase of Anxiety Level (AL) during the intervention. We will use a random intercept model, because we expect individual differences to exist in the levels of DC, AB, AL. Step 1. DC = b0 + b1*Group + b2*Time VG = b0 + b1*Group + b2*Time. Step2. AL = b0 + b1*Group + b2*VG + b3*DC. To test the third hypothesis (moderation by cognitive level), we will perform a multilevel analysis as above. 1st: Dysfunctional Cognitions (DC) and Avoidance Behavior (AB) will be dependent variables, in separate analyses. Cognitive Level (CL) will be added as predictor in a hierarchical linear multilevel model, including the interaction with condition to test for the moderating effect of CL on the relation between condition and mediators. Time will be added and modelled as T = 0,1,2,3,4, to tested the linear increase of DC and AB during the intervention. We will use a random intercept model, because we expect individual differences to exist in the levels of DC and AB. DC = b0 + b1*Group + b2*CL + b3*Group*CL + b4*Time VG = b0 + b1*Group + b2*CL + b3*Group*CL + b4*Time. The variable Cognitive Level (CL) will be centered at zero. For the follow-ups, when interaction effects appear to be significant, simple slopes plots will be made to illustrate the interaction effect. The 95% confidence interval of the parameter estimates of the multilevel and logistic regression analyses will be used to assess the statistical and practical significance of the estimates. The standardized parameter estimates will be used as estimated effect sizes. For all interval variables univariate outlier detection will be applied by using the Inter Quartile Range (IQR): scores outside 1.5*IQR will be examined, in order to see whether these are genuine scores, and cannot be attributed to coding or other errors. If they are genuine the scores remain in the analysis, otherwise they are removed from the analysis. Since we will use multilevel analyses drop-outs can be kept in the analysis. Subjects with at least one wave (time point) with complete data will be used in the analysis. No imputation strategy will be applied. We will explore the time factor in more detail. Other coding schemes than a simple linear coding will be tested to see whether effect gradually weaken in time or take effect after a certain period. Furthermore, we will explore whether the proposed model has predictive value for the binary outcome (anxiety diagnosis).

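### The printed mediation and cognitive-level models omit sex and age, the two stratification factors, which makes Group intervals too wide and leaves avoidable confounding on the mediator-to-anxiety paths

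*Protocol article*

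**What the plan says.** All references are to the Protocol article.

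- **Methods, Procedure (text after Fig. 2):** "We apply block randomization with child’s age and sex as strata".
- **Methods, Analyses, primary question:** "Sex and Age will be added as extra predictors", followed by "Model: AL = b0 + b1*Group + b2*Sex + b3*LC + b4*Group*Sex + b5*Condition*LC". LC is the age category.
- **Methods, Analyses, mediator models:** "Step 1. DC = b0 + b1*Group + b2*Time VG = b0 + b1*Group + b2*Time". VG stands where the text has avoidance behaviour (AB).
- **Methods, Analyses, outcome model:** "Step2. AL = b0 + b1*Group + b2*VG + b3*DC".
- **Methods, Analyses, moderation by cognitive level:** "DC = b0 + b1*Group + b2*CL + b3*Group*CL + b4*Time VG = b0 + b1*Group + b2*CL + b3*Group*CL + b4*Time".

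The mediation and moderation analyses are multilevel, with a random intercept per child and five assessments. No sentence brings sex or age into the last three sets of equations. The plan judges estimates by their 95% confidence intervals.

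**The concern.** Three features of the plan do not fit together.

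1. **Stratified allocation, unstratified models.** Stratifying balances the arms on age and sex, so the real chance variation of the Group estimate no longer contains their contribution. A model without the two factors still counts that contribution as noise and reports an interval that is too wide.
2. **Non-randomised paths.** Randomisation protects the effect of Group on the mediators. It does not protect the paths from dysfunctional cognitions and avoidance to anxiety. A fixed child characteristic that affects both a mediator and anxiety biases those paths. The random intercept does not remove it, because the coefficient also draws on differences between children. The Procedure section gives a reason to take sex seriously: the anxiety screening cut-offs differ for boys and girls, so anxiety at entry can differ by sex by design.
3. **Age and cognitive level.** Cognitive level comes from a 10-item task in children aged 8-13, with no age-norming described. The primary model allows the effect to vary by age category. The cognitive-level models do not, so a reader cannot tell how far a Group-by-CL result depends on age.

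Aims 3 to 5 (mediation, relative contribution of the mechanisms, moderation) are at stake. The primary model already contains both factors.

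**Working it through.** **The plan's own figure.** The article has no figure for this point. Its sample size of 240 comes from a simulation whose path values, residual variances and within-child correlation are not printed. It can be neither confirmed nor refuted, and nothing below depends on disputing it.

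**Inputs from the article:** 240 children, 120 per arm; five assessments; 10% drop-out between measurements; random intercept per child.

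**Assumed inputs, not in the article:** R2, the share of total variance explained by sex and age together, 0.03-0.10; ICC, the within-child correlation, 0.5-0.7.

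**Step 1. Reported standard error of Group.** Expected assessments per child: 1 + 0.9 + 0.81 + 0.729 + 0.656 = about 4.1. The variance of a child's mean is proportional to ICC + (1 - ICC)/4.1. Sex and age are child-level, so including them removes R2 from it:

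SE ratio = sqrt[(ICC - R2 + (1 - ICC)/4.1) / (ICC + (1 - ICC)/4.1)]

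- ICC 0.7, R2 0.03: sqrt(0.743/0.773) = 0.980, a 2% fall. In interval width this equals 1/0.980² = 1.04, or 4% more children.
- ICC 0.5, R2 0.10: sqrt(0.522/0.622) = 0.916, an 8% fall, equal to 1/0.916² = 1.19, or 19% more children.

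**Step 2. Simulation of the printed Step 1 and Step 2 models.** Settings: 240 children, five waves without drop-out, 1:1 allocation within four sex-by-age strata, 1,500 replications per setting. Assumed values: ICC 0.5; Group-to-mediator effect -0.2; mediator-to-anxiety effect 0.2, or 0 for the last column; direct effect -0.3. Sex and age act in the same direction on mediators and anxiety. Results with sex and age omitted, as printed (power also with both added):

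| R2 | Group SE: reported / actual (Step 1) | Group 95% CI coverage | Group power, omitted → added | Mediator path, true 0.2 | Its 95% CI coverage | False positives, true path 0 |
|---|---|---|---|---|---|---|
| 0 | 1.00 | 95.4% | 52% → 52% | 0.199 | 96.0% | not run |
| 0.02 | 1.01 | 95.5% | 53% → 55% | 0.207 | 94.7% | 5% |
| 0.05 | 1.04 | 95.9% | 50% → 55% | 0.217 | 89.9% | 9% |
| 0.10 | 1.10 | 96.3% | 54% → 60% | 0.233 | 78.7% | 21% |
| 0.20 | 1.24 | 98.3% | 52% → 69% | 0.267 | 35.2% | 66% |

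The R2 0.20 row lies outside the 3-10% range and only shows the trend. With sex and age added, at R2 0.02-0.20 the mediator path averages 0.200-0.201 with coverage 94.7-95.1%, and the ratio of reported to actual Group SE is 0.99-1.01.

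**Reading.** The actual spread of the Step 1 Group estimate is the same with and without the factors (0.0957 in both at R2 0.05). Only the reported SE changes, from 0.0997 to 0.0950. On the mediator path the reported SE is about right (0.0289 against an actual 0.0292 at R2 0.05), so the fault there is bias, not width.

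**Step 3. Group-by-CL.** Suppose only age moderates, by 0.2 SD per SD, and CL correlates 0.3-0.6 with age (all assumed). The printed model then shows a Group-by-CL coefficient of 0.2 × 0.3 = 0.06 to 0.2 × 0.6 = 0.12. Its standard error is sqrt[(ICC + (1 - ICC)/4.1) × 2/120]: sqrt(0.622 × 2/120) = 0.10 at ICC 0.5 and sqrt(0.773 × 2/120) = 0.11 at ICC 0.7. The coefficient is therefore about 0.5 to 1.2 standard errors.

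**The case against.** **The equations are shorthand.** Step 2 omits Time although the text says Time will be added, no random intercept is printed, Group and Condition are mixed, and avoidance appears under two abbreviations. A preregistered analysis plan exists and is not shown. This weakens the inference that sex and age were deliberately excluded. However, the text names both for the primary model and nowhere for the others. If the preregistered plan does include them, the article's equations should be aligned with it.

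**The interval error is harmless to validity.** This stands. A reader might infer that mismatched error bars inflate false positives for the intervention effect. They do not: Group coverage is at or slightly above 95%, and the loss is about 2 to 6 points of power at R2 0.02-0.10. The mismatch concerns Group terms only.

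**The confounding is unquantified.** This largely stands. A reader might infer that the mediation results are bound to be spurious. The documents give no R2 and no direction of effect. At R2 of about 2% the bias is negligible; opposite directions would reverse it; a factor unrelated to either mediator or anxiety does not confound.

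**The remedy is partial.** This stands too. Two covariates leave every other common cause of mediator and anxiety in place. Separating within-child from between-child mediator variation would go further against stable traits.

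**Age belongs to cognitive level.** A reader might infer that an unadjusted Group-by-CL term is an artefact and that CL should be age-standardised. The documents do not support this. Aim 5 concerns cognitive developmental level, and the background section on cognitive development justifies it with contrasts between age groups. Age-related variation is part of what CL is meant to capture; a standardised score would test relative ability, a different question. The absence of a Group-by-age term is therefore not an error.

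**Conclusion.** The concern holds in limited form. The omission is printed, it is inconsistent with both the randomisation and the primary model, and no reason is given for it.

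- **Group terms:** reported intervals are too wide if sex and age predict the outcomes. The reported SE could fall by about 2-8% at assumed R2 of 3-10% and ICC of 0.5-0.7. The error is conservative.
- **Mediator-to-anxiety paths in Step 2:** open to avoidable confounding whose size and direction the documents do not fix. Under the assumed values and a common direction of effect, it is negligible at R2 of about 2% and material from about 5%, where coverage falls to about 90% and false positives rise to about 9%.
- **Moderation by CL:** dependence on age is worth showing, but the planned test is not wrong.

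The mechanism and moderation aims are affected; the primary efficacy model is not. Confidence is high that the omission is in the text and moderate that it matters in size.

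**What to change.** 1. Add Sex and age category, coded as in the randomisation, as main effects to Step 1, Step 2 and both cognitive-level models.
2. State that the mediator-to-anxiety paths are not randomised and that confounding by other factors may remain after this adjustment.
3. As a sensitivity analysis only, also report Group*CL with a Group*age term added, to show how far the moderation result depends on age. Keep CL as measured; do not replace it with an age-standardised score.

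The cost is a line or two in the analysis plan. Both variables are already used for stratification and in the primary model, so no new data are needed. The sensitivity model will have a somewhat wider interval for Group*CL.

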CBT thus has a strong theoretical basis that is supported by empirical studies, convincingly demonstrating that CBT is currently an effective treatment for anxiety symptoms and anxiety disorders. To date, it is unknown whether CBT for children with anxiety actually works via decreasing dysfunctional cognitions and via decreasing avoidance. Studies on CBT’s working mechanisms in children are sparse. One of the most important prerequisites of examining working mechanisms is to establish that the outcome only changes after the active ingredients considered part of the working mechanisms has been offered [32]. This prerequisite is seldomly complied with. To our knowledge, mediation studies on child anxiety CBT are non-existent regarding online CBT and only a few mediation studies exist in which CBT was performed in a face-to-face format ([33]; P. C [34–37]). Of these face-to-face studies, only Hoogendoorn’s study (2014) meets the prerequisites of testing mediation [32]. Unfortunately, avoidance behavior was not taken into consideration in Hoogendoorn’s study. Therefore, we cannot draw firm conclusions on CBT’s effect on child anxiety via alteration of cognitions and avoidance behavior, and we cannot draw any conclusions about CBT’s working mechanisms when offered in an online format.

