Instead, inhibitory learning has been forwarded as a promising venue [38, 40, 41]. To grasp inhibitory learning, one must understand Pavlovian fear conditioning. When a neutral stimulus (conditional stimulus: CS) is repeatedly followed by an aversive stimulus (unconditional stimulus: US), in time a CS-US association is formed and the neutral stimulus will evoke an anticipatory fear reaction (conditional reaction: CR). This conditioned fear reaction can be decreased powerfully by extinction procedures, when the conditioned stimulus is repeatedly offered without the aversive stimulus (i.e. CS without US). Exposure is viewed as the clinical analogue of extinction, and inhibitory learning as extinction’s most important working mechanism. In contrast to habituation-based exposure, inhibitory learning does not specifically aim to reduce the anxiety levels of the person undergoing exposure. In fact, anxiety levels usually increase while applying inhibitory learning-based exposure. According to inhibitory learning models, an additional inhibitory association (CS – no US) is acquired in addition to the original CS-US association. Put simply, new information is learned that can override the old information. The extent to which new information can overrule the old information depends on the strength of the learning experience. Children who are at risk for developing anxiety disorders have deficits in inhibitory learning [40]. These deficits may hinder them from optimally profiting from exposure interventions. It is, therefore, important to create optimal inhibitory learning opportunities for anxious children in interventions. Strong learning experiences, in which the expectancy of the child about the feared situation is violated clearly and explicitly are seen as optimal inhibitory learning opportunities. This is why exposure based on inhibitory learning leans strongly on variability, and not on predictable steps of increasingly difficult exposure to the feared stimuli. During exposure based on inhibitory learning, variable stimuli, variable durations, variable levels of intensity of the exercise and variable levels of anxiety provocation are applied. Some child intervention studies for anxiety related difficulties already paid attention to making the child’s expectations about the feared situation explicit and monitoring and/or evaluating the child’s expectation during and after exposure ([42]; Philip C [43–47]). However, to our knowledge, no study exists that specifically applied variability in their exposure to create optimal inhibitory learning opportunities.

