### Learn to dare study

The current study has five aims. First, we examine the efficacy of ‘Learn to dare!’, an online CBT program that targets anxiety without parental support and minimal therapist support. We expect that the intervention ‘Learn to Dare!’ will decrease the anxiety levels of children stronger than the anxiety levels of children in the waitlist control group. Second, we study the efficacy of exposure based on the inhibitory learning model. It is expected that exposure based on inhibitory learning will decrease child anxiety levels than the anxiety levels of children in the waitlist control group. Third, we examine whether decreases in dysfunctional cognitions and avoidance behavior are CBT’s working mechanisms. We expect that a decrease in child CBT will be mediated by decreases in dysfunctional cognitions and avoidance behavior. Fourth, the relative contribution of both proposed working mechanisms is explored. Fifth, we study whether the child’s cognitive developmental level differentially affects the proposed working mechanisms. We expect that the child’s cognitive developmental level directly affects the decrease of dysfunctional cognitions, while it does not directly affect the decrease of avoidance. In case of a high cognitive developmental level, a synergistic positive effect of the working mechanisms is expected to take place (see Fig. 1). The study design is a randomized two-group factorial design with repeated measures of the dependent variables. Intervention versus control group makes the between subjects factor and time is the only within subjects factor.

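### Step 2 of the mediation analysis assumes the same mediator-to-anxiety slope in both arms and never checks it; add arm-specific slopes as a companion analysis

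*Protocol article*

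**What the plan says.** The mediation analysis (Protocol article, Analyses) has two steps. The mediator models are "Step 1. DC = b0 + b1*Group + b2*Time VG = b0 + b1*Group + b2*Time". The outcome model is "AL = b0 + b1*Group + b2*VG + b3*DC". VG is not in the abbreviation list; I read it as avoidance, because the surrounding prose names avoidance behavior as the second mediator. The random part is an intercept only: "We will use a random intercept model, because we expect individual differences to exist in the levels of DC, AB, AL".

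The same section does write interactions with condition elsewhere. The primary model has products of condition with sex and with age category. The moderation models add cognitive level, "including the interaction with condition to test for the moderating effect of CL on the relation between condition and mediators". None of these concerns the path from mediator to anxiety.

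The question being served is Aim 3 (Learn to dare study): "we examine whether decreases in dysfunctional cognitions and avoidance behavior are" the working mechanisms of CBT. The Background frames the gap in the same way: "it is unknown whether CBT for children with anxiety actually works via decreasing dysfunctional cognitions and via decreasing avoidance".

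**The concern.** Aim 3 concerns how the programme works in children who receive it. The path from programme to mediator comes from the randomised comparison. The path from mediator to anxiety is a regression slope, and Step 2 estimates it from both arms together under an unstated assumption that it is the same in each.

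Equality is not self-evident. In waitlist children, avoidance and anxiety move together as they do without intervention. In the intervention arm, avoidance is changed on purpose, through planned experiments aimed at one of two selected anxiety domains. If the slopes differ, mediation by avoidance could be concluded largely because untreated anxious children avoid more. Equally, a real pathway in treated children could be diluted by a weak waitlist slope. As the plan stands, the reader of the results could not tell.

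**Working it through.** **Inputs from the article.** 240 children, 120 per arm; 10% random drop-out between measurements; a medium direct and small indirect effect; 80% power for both pathways (Participants). Five assessments, T1 to T5 (Analyses), the same in both arms (Procedure).

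**Inputs assumed.** Arm-specific slopes, mediator variances, intraclass correlation (0.3 to 0.7), two-sided 5% level. None of these is given for this calculation.

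**The plan's own figure.** N = 240 cannot be reproduced exactly, because medium and small carry no numbers. It is plausible. After four 10% losses, 120 × 0.9⁴ = 78.7 per arm remain; at 0.5 SD this gives z = 0.5 × √(78.7/2) = 3.14 and power of about 88%, and the simulated repeated-measures analysis gives about 99% or more. Simulated power for the indirect path runs from 37% to 99% over first paths of −0.20 to −0.35 SD and slopes of 0.10 to 0.20. N is not in dispute here.

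**What the common slope estimates.** Let s be the waitlist share of the information on the slope:

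b_common = (1 − s) × b_CBT + s × b_WL

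With r = b_WL / b_CBT, the ratio of common to intervention-arm slope is 1 + s(r − 1). The first path is the same in either calculation, so this is also the ratio of the indirect effects. In simulation s = 0.499 with equal within-arm mediator variances, which gives (1 + r)/2:

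| r | ratio at s = 0.5 |
|---|---|
| 0 | 0.50 |
| 0.5 | 0.75 |
| 1 | 1.00 |
| 2 | 1.50 |
| 3 | 2.0 |
| 5 | 3.0 |

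**Dependence on the variances.** For intervention-to-waitlist variance ratios of 0.5, 1.5, 2 and 3, s is 66%, 40%, 33% and 25%. At r = 2 the ratio therefore runs from 1 + 0.25 = 1.25 to 1 + 0.66 = 1.66. At r = 0.5 it runs from 1 − 0.5 × 0.66 = 0.67 to 1 − 0.5 × 0.25 = 0.875.

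**Fitted models** (first path about −0.36 SD):

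- Slopes 0.15 (CBT) and 0.30 (WL): common slope 0.225, ratio 1.5.
- Slopes 0.30 and 0.15: common slope 0.225, ratio 0.75.
- Slopes 0 and 0.30: common slope 0.15, significant in over 99% of runs. Joint significance of both paths declares mediation in 92%. Group × mediator terms return an intervention-arm slope of about 0.
- Slopes 0.30 and −0.10: common slope 0.10, one third of the intervention-arm value.

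**Price of separate slopes.** In one simulation the slope's standard error rises from 0.027 to 0.038; 0.038/0.027 = 1.41. At a slope of 0.10, z falls from 3.7 to 2.6 and power from about 96% to 75%. A second simulation has an interaction standard error of 0.064. This implies 0.064/√2 = 0.045 per arm and 0.045/√2 = 0.032 pooled, and power of about 88% falling to 60%. Direct simulation under its own assumed variances gave about 89% falling to 64%. The smallest slope difference detectable with 80% power is 2.8 × 0.064 = 0.18.

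**Time.** The prose says Time will be added, but the printed Step 2 omits it. When effects built up over the waves and Time was left out, the interaction model gave an intervention-arm slope of 0.16 where the truth was 0.10. The companion model therefore needs Time as well.

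**The case against.** Group plus mediators as main effects is the standard product-of-coefficients model. With unequal slopes and equal weights it estimates the average of the two arms' indirect effects, and waitlist data are legitimate evidence for it. An indirect effect evaluated at the intervention-arm slope is one definition; one evaluated at the control-arm slope is another. The article commits to neither. All of this stands, and is why the common-slope model should stay.

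A reader might infer that the indirect effects will be misstated severalfold. The article has no input for that: threefold needs a waitlist slope five times the treated one under equal weights. A reader might also take it as fact that half of the evidence comes from untreated children. That holds only under similar residual mediator variances.

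The Inhibitory learning section says that "anxiety levels usually increase while applying inhibitory learning-based exposure". It is tempting to read this as evidence of unequal slopes. It concerns anxiety levels during exposure, not the relation between avoidance and questionnaire anxiety at the assessment points.

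The schedule also blurs the contrast. T1 follows session 1, before any exposure. With 10% loss per interval, T1 supplies 1/4.095 = 24% of intervention-arm observations, and T1 with T2 supply 1.9/4.095 = 46%. The Procedure places T2 before actual exposure, while the intervention description has a first experiment in session 3, so T2's status is uncertain. A treated slope of exactly zero is thus an extreme case, and one Group*VG term would still mix waves before and after exposure.

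Finally, the article condenses a preregistered plan that is not shown and may cover this. But the article prints the model explicitly, and nothing in its text adds the interaction.

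**Conclusion.** The point holds as an untested assumption behind a central aim, not as a demonstrated bias. Step 2 imposes equal mediator slopes across arms and the article describes no check. If the slopes differ by a factor of up to two in either direction, the indirect effect is about 0.75 to 1.5 times the one in treated children, given similar residual mediator variances (0.67 to 1.66 over the variance ratios tried). Larger errors need wider slope ratios, such as a treated slope near zero, or slopes of opposite sign. With equal slopes there is none. The slopes are assumptions throughout.

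The documents do not support calling the common-slope model wrong, or the intervention-arm slope the only correct target.

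**What to change.** Keep the common-slope Step 2. Pre-specify beside it a companion model that adds Group*VG and Group*DC, with both mediators centred and Time included as the prose states. Report each indirect effect at the intervention-arm slope and at the waitlist slope, with 95% confidence intervals, whatever the interaction p-value; the test is too weak to act as a gate. State in advance that the Aim 3 conclusion will be limited if the intervention-arm estimate does not support it.

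The cost is two model terms (plus Time, already announced) and no new data. The downside is precision: arm-specific slopes have standard errors about 40% larger. In a trial sized for small indirect effects, that is the reason not to make the companion the main analysis. It also does not remove confounding: mediator and anxiety are measured at the same time, and treated children who stay anxious may also avoid more.
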